#### Outcome measurement

We will use the EQ-5D-3 L and convert scores into quality-adjusted life years (QALYs) using linear interpolation and area under the curve methods for the trial period [36]. We will adjust for any baseline differences between treatment groups [37]. The main outcome for the cost utility analysis will therefore be incremental cost per QALYs estimated from the change in EQ-5D-3 L score at baseline and at 91 days follow-up, post-discharge.

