### Trial design

The study is a single-centre pragmatic parallel randomised controlled trial with an integral qualitative mechanism and action study and health economic study. Participants will be followed-up to 91 days post-discharge.

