### Secondary outcome measures

The secondary outcome measures are:Super spell bed days (total time in NHS care including hospital care and intermediate care) from admission to 91-day follow-up.Unplanned re-admission rates at day 28 and day 91. Days 28 and 91 were selected as they are the commissioners’ targets for re-admission.The Barthel ADL index [24] at baseline and at 91 days post-discharge to assess activities of daily living (ADL) and mobility.EQ-5D-3 L health-related quality of life measure [25] at baseline and at 91 days post-discharge. The EQ-5D-3 L is a standardized measure of quality of life looking at mobility, self-care, usual activities, pain and/or discomfort and anxiety and/or depression.The Charlson comorbidity index [26] at baseline and at 91 days post-discharge to assess comorbidity. The Charlson codes a total of 22 comorbid conditions into a single score.The mean cost per patient of CIRACT and THB-rehab will be estimated using micro-costing methods.The modified Client Service Receipt Inventory (CSRI) questionnaire [27] at baseline and at 91 days post-discharge. The CSRI is a cost questionnaire designed to measure and compare the service cost of both rehabilitation services.

The RA will collect demographic data (including age, sex, reason for admission and living circumstances) and outcome measures via face-to-face interviews on trial entry, and via a telephone interview at the three-month follow-up assessment. The RA will be blinded to treatment allocation. The time schedule of enrolment, interventions, assessments and visits for participants is shown in Additional file 1 and the trial flow diagram is presented in Figure 1.

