### Cost analysis

A detailed cost analysis of the two services to the NHS will be considered from a time and motion study, and compared against cost estimates based on standard methods of collecting resource use information (here via a modified Client Service Receipt Inventory (CSRI) questionnaire [27] at baseline and at 91 days post-discharge). The detailed micro-costing study will be conducted in three phases:A structured literature review (phase one): The review will provide information on how to conduct the time and motion study (phase three).Observation and semi-structured interviews (phase two): Observations and interviews will provide information on how to conduct the time and motion study (phase three) and define what activities are undertaken by each service. The observations of the therapists will enable a greater understanding of what each team offers and how they differ in their service provision. This will allow comparisons to be drawn between the two groups.Micro-costing study (phase 3): using the information from phase one and two a time and motion study will be conducted with 10 patients in each arm, recruited through purposive sampling, over a six-month period. Within each treatment arm, we will aim to include half of the participants with baseline admission Barthel ADL of less than 14, and the other half with a Barthel ADL of greater than 14, in order to ensure a wide range of abilities are observed. The time and motion study will record therapy interactions with the patient (face-to-face and indirect) to enable costing of each service provision. To get this data an RA will contact the ward therapists or the CIRACT team (depending on allocation) on a twice daily basis and ask how much time they have spent in direct face-to-face contact with the patient and indirectly, through non-face-to-face contact (ward rounds, telephone calls, referrals, and so forth).

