**Table 1 Tab1:** **Summary of major protocol amendments**

**Date of amendment**	**Wording pre-amendment**	**Wording post-amendment**
14 October, 2013	Follow-up at day 91 post-discharge face-to-face interviews by RA at participant’s home.	Follow-up at day 91 post-discharge.
		Telephone or face-to-face interviews by RA at participant’s home.
14 October, 2013	Follow-up to be completed at day 91 (+/− 3 days) post-discharge.	Follow-up to be completed at day 91 (−7/+28 days) post- discharge.
14 October, 2013	Patients excluded at discharge will be excluded from the length of stay (LOS) analysis, but a sensitivity analysis using proxy LOS models will be used to check the robustness of the exclusion.	The final intention-to-treat analysis will include all randomised participants for whom the follow-up assessment of the primary outcome measure is available. Per protocol analysis will include all randomised participants who are deemed to have no protocol violations.
14 October, 2013	Additional paragraph.	Modified client services receipt inventory: GP practices may be contacted by the research team to confirm visit data supplied by the participant.
10 March, 2014.	We propose to conduct the trial on two wards which will give the required numbers within our proposed timetable for the study.	We propose to conduct the trial on two to three wards which will give the required numbers within our proposed timetable for the study.
10 March, 2014.	Additional paragraph.	The RA will contact the therapist involved with looking after the patient at two time points during the day, from admission onto the ward until the patient is discharged from the ward, and continuing if applicable into the participant’s place of residence for a period of two weeks Data collected will be coded and entered into the database recording total time spent with the patient (face-to-face and non-contact). A summary of location codes will be extrapolated from phase two.

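### The QALY horizon is length of stay plus 91 days, so it depends on the primary outcome; on actual elapsed time the slower-discharge arm gains about 0.003 to 0.006 QALY with identical health

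*Protocol article*

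**What the plan says.** Under Trial design the article states: "Participants will be followed-up to 91 days post-discharge". Secondary outcome measures lists the "EQ-5D-3 L health-related quality of life measure [25] at baseline and at 91 days post-discharge", with the baseline interview held at trial entry. Under Outcome measurement in the health economic study, the team will "convert scores into quality-adjusted life years (QALYs) using linear interpolation and area under the curve methods for the trial period". The next sentences add "We will adjust for any baseline differences between treatment groups" and say that the cost-utility result is "estimated from the change in EQ-5D-3 L score at baseline and at 91 days follow-up, post-discharge".

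The other economic inputs end at the same point. Cost analysis collects resource use with the modified Client Service Receipt Inventory (CSRI) "questionnaire [27] at baseline and at 91 days post-discharge". Super spell bed days are defined as "total time in NHS care including hospital care and intermediate care) from admission to 91-day follow-up". Table 1 has "Follow-up to be completed at day 91" after discharge, with a current window of −7/+28 days.

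The primary outcome is length of stay from randomisation to discharge. The sample size section designs for a three-day reduction, given as a ratio of geometric means of 0.7, with a log-scale standard deviation of 0.9. The article states no fixed horizon from randomisation, no common truncation day and no correction for unequal duration.

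**The concern.** An area under a utility curve grows with the time it covers. Here the curve starts at trial entry and ends at a day counted from discharge, so a patient who stays three days longer contributes three more days of area. The length of the measurement period is thus set by the outcome that randomisation is expected to change. If the service works as hoped, its arm is credited with less time alive in the QALY total, although nobody's health differs.

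Adjusting for baseline EQ-5D does not repair this. The imbalance arises after randomisation and lies in duration, not in starting utility. An incremental cost per QALY divides by a small difference between two totals of roughly 0.14, so a systematic shift of a few thousandths can move the ratio materially. The economic result is meant to tell commissioners whether to provide the service.

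**Working it through.** The article gives no QALY figure to reproduce. The check uses its design effect and time points, and does not depend on the sample size.

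**Inputs from the article**
- End of follow-up: 91 days after discharge (Trial design).
- Effect: three days, ratio of geometric means 0.7; log SD 0.9 (Sample size calculation).
- Recent local mean stay: nine days (Background).

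**Assumption:** the same mean utility *u* in both arms, 0.5, with a range of 0.3 to 0.7.

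**Stays implied by the design effect**
- Geometric means: 3 / (1 − 0.7) = 10 days, against 10 × 0.7 = 7 days.
- QALYs and costs are compared on arithmetic means. For a log-normal variable, arithmetic mean = geometric mean × exp(SD²/2), and exp(0.81/2) = 1.499. This gives 15.0 v 10.5 days, a gap of about 4.5 days.
- If nine days is instead the control arm's arithmetic mean: 9 v 9 × 0.7 = 6.3 days, a gap of 2.7 days.

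**Formula:** QALY = *u* × (stay + 91) / 365.25. With equal utilities, the difference between arms is *u* × gap / 365.25.

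| Stays (days) | Horizons (days) | Spurious gain, slower arm, *u* = 0.5 | *u* = 0.3 to 0.7 | Relative |
|---|---|---|---|---|
| 9 v 6.3 | 100 v 97.3 | 0.0037 | 0.0022 to 0.0052 | 2.8% |
| 10 v 7 | 101 v 98 | 0.0041 | 0.0025 to 0.0058 | 3.1% |
| 15.0 v 10.5 | 106.0 v 101.5 | 0.0062 | 0.0037 to 0.0086 | 4.4% |

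At *u* = 0.45 and a gap of 2.7 days the result is 0.45 × 2.7 / 365.25 = 0.0033, so 0.003 to 0.006 covers utilities near 0.5.

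**Scale.** At 10 v 7 days the totals are 0.5 × 101 / 365.25 = 0.1383 and 0.5 × 98 / 365.25 = 0.1342. To cancel the artefact, the faster arm needs a mean utility of 0.5 × 101/98 − 0.5 = 0.015 more. With the same baseline, that is about 0.031 more at follow-up. For 15.0 v 10.5 days the figures are 0.022 and 0.044.

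**Same health, one fixed horizon.** If utility is constant and equal, every participant contributes the same number of days and the artefact is zero. If utility changes, a small dependence remains, because the second measurement still falls at stay + 91. Suppose utility rises by 0.2 in both arms, with stays of 10 v 7 and the curve cut at day 91 from randomisation. The difference is 91 × 0.1 × 91 × (1/98 − 1/101) / 365.25 = 0.0007 QALY, now favouring the faster arm.

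**The case against.** The strongest reply is that the article does not say how duration enters the calculation, and a condensed article may leave that to the analysis plan. Two other readings are possible:

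- Everyone is given a nominal 91 days. The artefact disappears, but the inpatient period, where the two services differ most, drops out of the QALYs.
- Only the change in EQ-5D is integrated, as the last sentence of Outcome measurement could be read. The sign then follows the change. With stays of 15.0 v 10.5 days, a rise from 0.3 to 0.6 gives the slower arm 0.15 × 4.5 / 365.25 = +0.0018, and a fall from 0.6 to 0.4 gives it −0.1 × 4.5 / 365.25 = −0.0012.

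This part of the reply stands: a bias of fixed direction follows only if elapsed time is used and mean utility is positive. It does not clear the plan, because the time points and the area method are stated, the article adopts neither alternative explicitly, and applying the method to the stated time points gives unequal horizons.

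It is also fair to say that costs and super spell days differ from QALYs. The longer index stay there is a real effect that ought to be counted, and both arms have the same nominal 91 days after discharge. The artefact is confined to the few extra days observed. It adds bed days and cost to the slower arm, so it works in the opposite direction to the QALY artefact.

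Finally, the effect is small in absolute terms, and nothing in the article shows that it would reverse a funding decision.

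**Conclusion.** The point holds for QALYs. With the stated time points and area method on actual elapsed time, the horizon is stay + 91 days, and the slower-discharge arm gains about 0.003 to 0.006 QALY (3% to 4%) with identical health. This rests on an assumed mean utility near 0.5 and on the design effect being realised. Utilities of 0.3 to 0.7 widen the range to 0.002 to 0.009. For costs and super spell days the point is limited to the extra days of observation.

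Three stronger inferences are tempting, but the article does not support them:

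- **The interview window biases the arms.** The −7/+28 days spread individual horizons over 35 days, but nothing suggests that interview timing differs by arm. This is noise.
- **Deaths drop out of the QALYs.** The rule against imputation stands in the general statistical section. Zero utility after death is a known value, not an imputed one, and the economic sections do not say that deaths are excluded.
- **Interviews at day 84 miss later readmissions.** Readmission is defined at days 28 and 91, and the article does not say that it is ascertained only at the interview.

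**What to change.** In the primary economic analysis, calculate QALYs to one fixed day from randomisation in both arms, for example day 91, interpolating EQ-5D-3L with each participant's actual randomisation and interview dates. Count super spell days to the same fixed day. Bring CSRI costs to that day as well, apportioning where contacts are not dated. Keep the discharge-anchored calculation as a sensitivity analysis, and leave the day 28 and day 91 readmission rates as they are.

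Randomisation and discharge dates are already needed for the primary outcome, and interview dates are needed to apply the window, so the QALY change needs no new data and no extra contact. The costs are modest:

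- An interview at day 84 after discharge falls before day 91 from randomisation only when the stay is under seven days, so extrapolation is never more than seven days.
- The article does not say that CSRI contacts are dated, so some costs would rest on apportioning.
- The new end point for super spell days alters a stated secondary outcome and should be recorded as an amendment.
- A residual dependence on stay remains, about 0.0007 QALY if utility rises by 0.2.

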#### Economic analysis

The results of the analysis will be presented using the incremental cost effectiveness ratio (ICER), if appropriate, with decision uncertainty represented via cost effectiveness acceptability curves (CEACs) based on nonparametric bootstrapping of cost and effect pairs [38]. This will provide robust results to inform decision-makers about whether the NHS should provide the CIRACT service or not compared to traditional care.

### Data collection

Data will be collected using CIRACT trial data collection forms which will be monitored by the Nottingham Clinical Trials Unit (NCTU) for consistency, validity and quality. Missing data and data queries will be referred promptly back to the recruiting site for clarification. If a participant withdraws from the study, the data collected up to that point will be used (as specified in the consent form) but no further data will be collected about that participant. Participants will not be replaced if they withdraw from the study. All reasonable attempts will be made to contact any participant lost to follow-up during the course of the trial in order to complete assessments.

### Data management

All trial data will be entered on a trial-specific database with participants identified only by the unique trial number, date of birth and initials. The database will be developed and maintained by the trial coordinating centre at the NCTU. Access to the database will be restricted and secure. Data quality and compliance with the protocol will be assessed throughout the trial by verification of trial data against clinical records, and by data checking for accuracy and internal consistency. For the follow-up phase, identifiable information about participants will be held in a separate database to the trial anonymised data. Access to this information will be restricted to those involved in the follow-up phase, as authorised by the Chief Investigator.

### Statistical analyses

The analysis and reporting of the trial will be in accordance with the Consolidated Standards of Reporting (CONSORT) guidelines. A full statistical analysis plan will developed before any data are analysed. Appropriate descriptive statistics will be used to compare the characteristics of the randomised participants across the trial groups. The primary approach to all comparative analyses will be based on treatment allocated without imputation of missing data. Between-group differences will be estimated using regression models appropriate for outcome type, adjusting for baseline value of the outcome if collected, and paying attention to 95% confidence intervals as well as *P* values. Analysis of subgroups will be agreed with the Trial Steering Committee and all those undertaken will be reported.

### Data monitoring

The day-to-day management of the trial is the responsibility of the Trial Manager, including research staff training and management. Regular monitoring will be performed by the trial Manager according to the Medical Research Council (MRC) Guidelines for Good Clinical Practice (GCP) in Clinical Trials (22). Following written standard operating procedures, the Trial Manager or where required, a nominated designee of the Sponsor, will verify that the clinical study is conducted and data are generated, documented and reported in compliance with the protocol GCP guidelines and the applicable regulatory requirements.

The study finance, documentation (such as assessment forms and operating procedures), data recording and storage is managed by the Trial Manager, who also monitors progress and provides appropriate reports to the Trial Steering Committee. The Principal Investigator will instigate audits of procedures as required and takes overall responsibility for any protocol changes throughout the study.

As the trial is regarded as low risk, the Trial Steering Committee will also act as the trial management group, and the data monitoring committee. The group will be chaired by the Principal Investigator, and will be comprised of investigators, research staff and patient representatives and will monitors all aspects of the conduct and progress of the trial, ensures that the protocol is adhered to, and will take appropriate action to safeguard participants and the quality of the trial.

In the case of an adverse event, the Trial Manager will receive adverse event forms electronically and the group will meet as required in the event of an excessive serious adverse event rate, or if other information is reported to it which raises concern over the safe conduct of the trial. There is no plan for any interim analyses.

### Harms

Data shall be collected for each individual participant with regards to any fall that occurs whilst an inpatient on the ward until time of discharge, and will be classed as an ‘adverse event’. If the fall results in a fracture, confirmed by radiological findings, it will be classed as a ‘serious adverse event’. This was agreed by the Trial Steering Committee. All serious adverse events will be reported to the sponsor within 24 hours of knowledge of the event using the adapted Nottingham University Hospitals NHS Trust reporting forms made specific to this study. The adverse event risks of taking part in the trial is minimal, as the CIRACT service is not a different type of rehabilitation, but a change in delivery of the THB-rehab service the patients would receive as part of their usual care. The CIRACT service has been assessed in a pilot study and no adverse events occurred.

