### Study intervention

Each participant will be randomly allocated to the CIRACT service (intervention arm) or THB-rehab (control arm). The CIRACT team will conduct an assessment of the participant’s ability to perform certain tasks within 24 hours of randomization, enabling the formulation of a comprehensive rehabilitation plan. The CIRACT team will consist of a physiotherapist, an occupational therapist and a community care officer who will be employed by Nottingham CityCare, but will be based on one of the study wards. While in hospital the participants will be treated daily (seven days a week, if appropriate) by the CIRACT team and the time of rehabilitation they receive will be dependent on their needs. During the participant’s hospital stay the CIRACT team will liaise with the participant and their carer(s) to visit the participant’s home to assess and provide recommendations for equipment and make adaptations and/or modifications if required. The CIRACT service will utilise the teams’ expertise in community working to form links with the appropriate services to ensure a smooth and effective discharge. In more complex cases the CIRACT team will take the participant out of the hospital for a home visit prior to discharge. Following discharge, the CIRACT team will visit the participant at home within 48 hours of discharge to assess the level of rehabilitation required at home, and the CIRACT team will undertake further follow-up visits as deemed necessary.

The THB-rehab service will be provided by the hospital-based therapy teams on weekdays only as a control group receiving ‘usual care’. Members of these teams will jointly conduct an assessment of the participant’s ability to perform certain tasks and provide recommendation for rehabilitation. The ward team will refer the participant to the appropriate community-based services for the provision of equipment at home, personal care and ongoing rehabilitation where appropriate at discharge. Once discharged from hospital, the patient will have no contact with the ward rehabilitation staff.

In either group, if a participant becomes medically unwell at any point to the extent they are no longer able to undertake therapy (as directed by the ward doctor), the treating team will withhold further therapy until being instructed by the ward doctor it is safe to recommence therapy. The nursing and medical care provided by the ward staff will not differ between the two groups.

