### Primary outcome measures

The primary outcome is hospital length of stay from randomisation to discharge from a general medical elderly care ward. The date of randomisation will be used instead of date of admission to the ward to negate for the impact of a delay in randomisation and reduce the risk of cross contamination.

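### Adverse events are collected only as in-patient falls up to ward discharge, a window set by the primary outcome; later falls, fractures and deaths are not listed

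*Protocol article*

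**What the plan says.** The Harms section of the protocol article collects "any fall that occurs whilst an inpatient on the ward until time of discharge" and calls this an adverse event. It then adds: "If the fall results in a fracture, confirmed by radiological findings, it will be classed as a" serious adverse event. No other event is placed in either class. The section says the Trial Steering Committee agreed the definition, and argues that risk is minimal because CIRACT changes how rehabilitation is delivered and not its type.

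Under Primary outcome measures: "The primary outcome is hospital length of stay from randomisation to discharge from a general medical elderly care ward". Under Trial design: "Participants will be followed-up to 91 days post-discharge". Under Study intervention: "Following discharge, the CIRACT team will visit the participant at home within 48 hours of discharge", with more visits as needed. Control participants have no contact with the ward rehabilitation staff once they leave hospital.

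The secondary outcomes do reach past discharge. They include "Unplanned re-admission rates at day 28 and day 91", super spell bed days to the 91-day follow-up, and the Barthel index and EQ-5D-3L at 91 days.

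On oversight, the Data monitoring section says that "the group will meet as required in the event of an excessive serious adverse event rate". The same sentence gives a second, open-ended ground: any other report that casts doubt on the trial's safe conduct.

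**The concern.** There are two linked problems.

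1. **The time at risk for an adverse event is the primary outcome.** Both end at ward discharge. An arm that sends patients home sooner has fewer days on which an in-patient fall can be counted, whatever its effect on fall risk. A report of shorter stay with fewer falls could then be one finding stated twice.

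2. **The window closes where the harm of earlier discharge would begin.** The trial is powered to detect a shorter stay in people aged 70 and over, and the Background itself describes the period around transfer home as one in which safety is often compromised. Falls, fractures and deaths after discharge appear in neither the outcome list nor the adverse event definition.

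The second problem is one of data collection. An analysis plan can choose how to analyse in-patient falls, but it cannot recover events that nobody recorded.

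**Working it through.** The article gives no figure for harms, so there is none to reproduce.

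**Inputs**
- Ratio of geometric mean stays, CIRACT to control: 0.7 (Sample size calculation).
- Randomised: 240 with equal allocation, so 240 / 2 = 120 per arm (Sample size calculation; Randomisation procedure).
- Control mean stay: 9 days. This is the local ward mean by 2013 (Background), used for illustration only.
- Fall rate: not in the article. Assumed equal in both arms at 8 per 1,000 bed days, with a range of 3 to 15.

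**Step 1: ratio of expected counts.** Expected falls = patients × mean stay × daily fall rate. If stay is log-normal with the same log-scale SD in both arms, the ratio of arithmetic means equals the ratio of geometric means, 0.7. With equal patients and equal daily rates, the ratio of expected falls is also 0.7, so the raw count is 1 − 0.7 = 30% lower in CIRACT with no true difference in risk. The assumed fall rate cancels out of this ratio.

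**Step 2: what the artefact could hide.** Raw counts would be equal only if the daily fall rate in CIRACT were 1 / 0.7 = 1.43 times that in control.

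**Step 3: expected counts.** Control bed days: 120 × 9 = 1,080. CIRACT: 1,080 × 0.7 = 756.

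| Assumed falls per 1,000 bed days | Control | CIRACT |
|---|---|---|
| 3 | 3.2 | 2.3 |
| 6 | 6.5 | 4.5 |
| 8 | 8.6 | 6.0 |
| 10 | 10.8 | 7.6 |
| 15 | 16.2 | 11.3 |

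At 8 per 1,000 the difference is 8.64 − 6.05 = 2.6 falls, against a Poisson standard error of √(8.64 + 6.05) = 3.8.

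**Step 4: do the listed post-discharge outcomes fill the gap?**
- *Unplanned re-admission* counts a fall or fracture that leads to an admission, but does not identify it as such and misses those not admitted. A patient who dies at home cannot be re-admitted.
- *Super spell bed days* stop accruing at death, so excess deaths can make an arm look better.
- *Barthel and EQ-5D-3L at 91 days* exist only for survivors, and the Statistical analyses section makes its primary approach one without imputation.

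Each outcome is informative about harm, but none can be read safely unless mortality is reported beside it.

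**Step 5: oversight.** The named rate can contain only fractures from in-patient falls, because that is the whole serious adverse event definition. The second ground for meeting is open, but no systematic route by which post-discharge harm would reach the group is described. Informal reports could also be uneven, since the CIRACT team visits at home while the control arm's ward team has no further contact.

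**The case against.** The strongest reply has five parts.

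- **Harms of earlier discharge are compared.** A reader might infer from the Harms section that they never are, or that the 91 days after discharge carry no harm data. The article does not support that. Unplanned re-admission is a direct check on premature discharge, and function and quality of life are measured at day 91. What stands is that these are indirect and exposed to distortion by death.
- **The oversight group can act on deaths.** A reader who stops at the serious event rate might infer that it cannot. The rest of the sentence allows it. What stands is the lack of any described systematic reporting.
- **No raw comparison of falls is planned.** Falls are not a listed outcome, regression models suited to the outcome type are promised, and a rate per bed day could be calculated from data already held. This is correct. It makes the 30% conditional, and the choice of count or rate belongs to the analysis plan. It does not help with events after discharge.
- **The numbers are small.** A difference of 2.6 falls with a standard error of 3.8 is well within chance. This is fair: the illustration shows the direction of the bias, not a result likely to reach significance.
- **The definition was deliberate, and the full protocol may hold more.** The committee agreed it for a trial regarded as low risk, and deaths may be recorded under the full protocol or analysis plan, neither of which is shown. This limits what can be said about mortality. It does not change the collection rule that the article states, and the rationale offered does not address earlier discharge.

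**Conclusion.** The point holds in a limited form. As the article states it, adverse event collection ends at ward discharge, so its length is the primary outcome. Post-discharge falls, fractures and deaths are not listed as outcomes or adverse events, and such harm is visible only indirectly.

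The size of the exposure effect is a 30% lower raw count of in-patient falls. It rests on a true stay ratio of 0.7, equal log-scale SDs, equal daily fall rates and an analysis of raw counts. Only the illustrative counts depend on the assumed fall rate. No size can be put on the unrecorded post-discharge harm, because the article gives no rates for it.

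This does not threaten the primary analysis. It limits what the trial can say about the safety of earlier discharge, and it is cheap to improve.

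**What to change.** Amend the Harms section and the sections tied to it:

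1. Record falls, fall-related fractures and all-cause death in both arms from randomisation to the day-91 contact, using the existing interview and the hospital record.
2. List all-cause mortality to day 91 as a safety outcome, and present it beside re-admission, bed days, Barthel and EQ-5D-3L.
3. Report in-patient falls per 1,000 bed days with a between-arm rate ratio.
4. Give the oversight group deaths and unplanned re-admissions alongside serious falls.

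Because day 91 is counted from discharge, the longer window still varies a little with stay. On the illustrative figures it is 9 × 0.7 + 91 = 97.3 days against 9 + 91 = 100 days, a gap of 2.7% in place of 30%. Dating events and using person-time removes that remainder.

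The cost is a few added interview items, one record check per participant and a small amendment. The contact already takes place, and the Data management section already provides for checking trial data against clinical records. The main drawback is imperfect recall of falls at 91 days; the hospital record is a partial check for events that led to hospital care.
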